### Outcome measures

The primary endpoint with respect to the efficacy of the standardized short-term EMDR intervention for CBP is the change in the intensity of back pain from T_0_ to T_1_ measured on a numeric rating scale (NRS 0–10, averaged over four weeks). The NRS for pain intensity has proven to be a reliable and valid instrument for assessing treatment effects in pain trials [55].

The secondary outcomes, which include distinct pain variables (mean pain duration, pain experience, and pain intensity at T_2_), medication intake, health-related quality of life (SF-12), anxiety and depression (HADS), dissociation symptoms (FDS-20), psychological resilience (RS-11), and somatization (SCL-90R subscale somatization), will be measured at all assessment points (T_1_ and T_2_).

In addition to the efficacy endpoints, we assess the peripheral and central modulation of pain (quantitative sensory testing, QST, and conditioned pain modulation, CPM) in all the patients to explore the differences in pain processing induced by the EMDR intervention. An overview of the primary and secondary outcomes is shown in Table 2.

**Table 2 T2:** Outcome measures

**Primary outcome**	
**Pain intensity**	• *Numerical rating scale (NRS)*, ranging from 0 ‘no pain’ to 10 ‘worst pain imaginable’ [55].
**Secondary outcomes**	
**Pain dimensions**	• *Pain duration* (number of painful days in the last 4 weeks).
	• *Pain Experience Scale (SES)* measures the affective and sensory dimensions of pain [56].
**Medication**	• Change in medication intake.
**Disability**	• *12-Item Short Form Health Survey (SF-12)* measures health-related quality of life [57,58].
**Depression and Anxiety**	• *Hospital Anxiety and Depression Scale (HADS-D)*[59].
**Stress/ Trauma**	• *Change in Posttraumatic Diagnostic Scale levels (PDS)*[60]*.*
	• *Dissociation symptoms questionnaire (DES/FDS-20)* for assessment of dissociative symptoms [61].
**Somatization**	• *Somatization scores* of the SCL-90R subscale somatization (SCL-90R) [62].
**Somato-sensory function**	• *Quantitative Sensory Testing (QST)* for assessment of all relevant aspects of the somatosensory system including large and small fiber function as well as signs of central sensitization (dynamic tactile allodynia, punctate mechanical hyperalgesia) [63].
**Conditioned pain modulation**	*• Conditioned Pain Modulation (CPM)* paradigm for assessment of inhibitory pain modulating mechanisms [64]. Difference in pressure pain threshold before and after inducing CPM by a phasic heat pain stimulus will be measured.

Moreover, as part of the LOGIN study, all the participants in our study will be assessed for a shared core set of variables, including a comprehensive assessment of neuromodulators (plasma nerve-growth-factor, plasma endocannabinoid and lipid levels) and the functional and structural changes in functional neuroimaging (fMRI), before and after treatment (for further details, see [43]).

### Assessment of safety

Serious adverse events (SAEs) will be documented and reported casuistically.

### Sample size estimation

The sample size calculation is based on the primary efficacy endpoint: change in the pain intensity (numeric rating scale 0–10) after the intervention (T_1_). The expected effect size for our trial is derived from previous evidence about the effect of EMDR therapy for chronic pain patients.

The two controlled trials currently available are characterized by high effect sizes with Hedges’ g ranging from −1.12 [65] to −6.87 [66]. Based on this data, an effect size of at least 1.0 can be expected after ten sessions of treatment. A sample size of 17 patients in each group will have 80% power to detect an effect size of 1.0 using a t-test for independent groups with a 0.05 two-sided significance level. Based on comparable studies and our own experience with pain trials, we expect a 20% drop-out rate. Therefore, a total sample size of 40 patients is required for the study. The patients who are lost to follow up and/or non-compliant patients will be handled using an intention-to-treat procedure.

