### Design

The study is designed as a randomized controlled trial with two parallel arms (see Figure 1). Forty patients will be randomized to either the treatment group (n = 20) or the control group (n = 20). The treatment group will receive EMDR in addition to TAU. The control group will receive TAU alone.

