### Statistical analyses

The data analysis will follow the evaluation standards for experimental study designs with control groups, using descriptive methods as well as inferential statistics. The data will be analyzed using an intention-to-treat approach. Because of the small sample size in the study, multiple imputation (the gold standard for handling missing values) is not appropriate. Therefore, only complete cases will be used in the final analysis. Dropouts, withdrawals and missing values will be analyzed in detail; different techniques will be used to assess them, and these techniques will be compared using sensitivity analyses. Descriptive statistics will be presented as the means and standard deviations for the continuous variables and absolute numbers and percentages for the categorical variables. The questionnaires will be processed in accordance with questionnaire manuals.

The differences between the change scores of the patient groups will be analyzed using independent t-tests. Moreover, potential negative effects will be reported descriptively (e.g., pain intensity after the trauma-focused intervention > pain intensity before the trauma focused intervention). Preliminary effect sizes will be estimated using Cohen’s d.

Pre-processing analyses and statistical analyses of quantitative sensory testing data will be performed according to the protocol used by Rolke et al. [63]. To quantify conditioned pain modulation, the pressure pain threshold before a phasic heat stimulus will be subtracted from the pressure pain threshold after the phasic heat stimulus. A negative value indicates an analgesic effect due to CPM [64].

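### Minor arithmetic error in the drop-out allowance: 40 patients cover 15% drop-out, not the stated 20%, so complete-case power at an effect size of 1.0 is about 78% rather than 80%

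*Protocol article*

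**What the plan says.** The Sample size estimation section builds the number on the change in back pain intensity up to T1. It takes its effect size from two earlier controlled trials: "Based on this data, an effect size of at least 1.0 can be expected after ten sessions of treatment". It then states: "A sample size of 17 patients in each group will have 80% power to detect an effect size of 1.0". The test named there is an independent-groups t-test at the two-sided 0.05 level. Next it says that "we expect a 20% drop-out rate", and from these inputs it draws the total: "Therefore, a total sample size of 40 patients is required for the study".

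The Design section repeats the figure: "Forty patients will be randomized to either the treatment group (n = 20) or the control group (n = 20"). The abstract gives the same numbers, and the Participants section makes 40 the point at which recruitment stops.

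On missing data, the Sample size estimation section says that patients lost to follow-up or non-compliant will be handled by an intention-to-treat procedure, and it names no method. The Statistical analyses section is specific. It rules out multiple imputation because the sample is small and states that "only complete cases will be used in the final analysis". Groups are to be compared on change scores with independent t-tests.

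**The concern.** The total is introduced as a consequence of two inputs, 17 evaluable patients per group and 20% drop-out, and it does not follow from them. Taking 20% from 40 leaves fewer than the 34 that the same paragraph requires.

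The gap would not matter if patients without T1 data still contributed to the primary comparison. Under a complete-case t-test they contribute nothing, so the drop-out allowance alone has to protect the power. What is at stake is whether the stated 80% is true of the design as described. No estimate, test or error rate is affected.

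**Working it through.** **Inputs, all from the protocol article.** Effect size d = 1.0; independent-groups t-test; two-sided significance level 0.05; 80% power; 17 per group; 20% drop-out; 40 randomised 1:1 (Sample size estimation and Design). Complete cases only in the final analysis (Statistical analyses).

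**Step 1: reproduce the plan's 17 per group.** For n per group, the test statistic follows a noncentral t distribution with 2n − 2 degrees of freedom and noncentrality d·√(n/2). Solving for 80% power at d = 1.0 gives n = 16.7, so 17 per group, with power 80.7%. The plan's figure is right.

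**Step 2: inflate for drop-out.** If a fraction q is lost, the number to randomise is n/(1 − q).
- Per group: 17/(1 − 0.20) = 21.25, so 22 per group and 44 in total.
- On the total: 34/0.80 = 42.5, so 43, or 44 once the arms are kept equal.
- Stated: 40, which is 3 to 4 patients fewer.

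**Step 3: what 40 delivers at 20% drop-out.** 40 × 0.80 = 32 complete cases, 16 per group, against 34 required.

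**Step 4: drop-out that 40 can absorb.** 1 − 34/40 = 15%.

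**Step 5: power at d = 1.0 with the completers.**

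| Completers per group | Power |
|---|---|
| 17 / 17 | 80.7% |
| 16 / 16 | 78.1% |
| 17 / 15 | 78.0% |
| 18 / 14 | 77.5% |
| 20 / 12 | 75.5% |

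The last three rows keep the total at 32 and show uneven loss, an illustrative assumption because the article does not split the drop-out by arm. With 16 per group, 80% power is reached at d = 1.02.

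**Step 6: other routes to 40.**
- Multiplying instead of dividing: 34 × 1.2 = 40.8, which rounds up to 41; per group, 17 × 1.2 = 20.4 rounds up to 21, or 42 in total. The total version comes close to 40, so rounding it down may be where 40 came from. The article does not say.
- The normal approximation: 16 per group, and 16/0.8 = 20 per group, which is exactly 40. But the article states 17 per group and a t-test.

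**The case against.** The strongest case on the other side concerns size. A loss of 1.9 points of power with equal drop-out is small. The plan expects an effect of at least 1.0, which it sets below the smaller of the two cited effects (Hedges' g of −1.12; the other is −6.87). At d = 1.12, 16 per group give 86.5% power. The difference between detecting 1.00 and 1.02 is trivial beside the uncertainty in an effect size drawn from two trials that far apart. All of this stands, and it is why the point is minor. It does not make the derivation correct, because the article's power statement is made at 1.0.

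A second objection is that the intention-to-treat wording keeps lost patients in the analysis. It does not stand: no method is named there, and the Statistical analyses section fixes complete cases. The sensitivity analyses promised in that section compare ways of handling missing values; they do not enlarge the primary sample.

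A third is that a fuller protocol or a separate analysis plan may give more detail. That would answer an omission. Here the inputs and the result are all printed, and they disagree.

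A reader might infer something stronger, that the trial is materially underpowered or that more patients must be enrolled. The figures do not support that: at the plan's own effect size and drop-out rate, power is still about 78%. Nor does the article support a probability of falling short of 34 completers. It gives one expected drop-out rate and no model of how drop-out varies, and it sets no minimum number of completers per arm.

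**Conclusion.** The concern holds as a minor arithmetic error. On the plan's own inputs, 40 should read 44 with equal arms (43 if only the total is inflated). Alternatively, the power attached to 40 should read about 78%. The shortfall is two completers in total, one per group, and 1.9 points of power at d = 1.0 with equal loss. If the 32 completers were split as unevenly as 20 and 12, it would be 4.5 points (80 − 75.5).

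The conclusion rests on the article's effect size, test and drop-out rate taken as given, and on drop-outs having no T1 value and so leaving the complete-case analysis. Whether 1.0 is a well-founded effect size is a separate question and is not judged here.

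**What to change.** Replace the concluding sentence of the Sample size estimation section with wording such as: 40 randomised patients leave 32 completers at 20% drop-out, giving about 78% power for an effect size of 1.0 with the two-sided 0.05 t-test; 80% power is reached only if drop-out is at most 15%. Add that 44 patients, 22 per group, would be the number consistent with both 80% power and 20% drop-out.

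This costs one sentence and a slightly less favourable power statement. It needs no extra patients and no change to the analysis. Moving to 44 would mean recruiting four more patients and changing the figure in the abstract, Design and Participants sections; a shortfall of this size does not require that.

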### Statistical analyses

The data analysis will follow the evaluation standards for experimental study designs with control groups, using descriptive methods as well as inferential statistics. The data will be analyzed using an intention-to-treat approach. Because of the small sample size in the study, multiple imputation (the gold standard for handling missing values) is not appropriate. Therefore, only complete cases will be used in the final analysis. Dropouts, withdrawals and missing values will be analyzed in detail; different techniques will be used to assess them, and these techniques will be compared using sensitivity analyses. Descriptive statistics will be presented as the means and standard deviations for the continuous variables and absolute numbers and percentages for the categorical variables. The questionnaires will be processed in accordance with questionnaire manuals.

The differences between the change scores of the patient groups will be analyzed using independent t-tests. Moreover, potential negative effects will be reported descriptively (e.g., pain intensity after the trauma-focused intervention > pain intensity before the trauma focused intervention). Preliminary effect sizes will be estimated using Cohen’s d.

Pre-processing analyses and statistical analyses of quantitative sensory testing data will be performed according to the protocol used by Rolke et al. [63]. To quantify conditioned pain modulation, the pressure pain threshold before a phasic heat stimulus will be subtracted from the pressure pain threshold after the phasic heat stimulus. A negative value indicates an analgesic effect due to CPM [64].

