**Methods/design:**

The study will recruit 40 non-specific CBP patients who have experienced psychological trauma. After a baseline assessment, the patients will be randomized to either an intervention group (n = 20) or a control group (n = 20). Individuals in the EMDR group will receive ten 90-minute sessions of EMDR fortnightly in addition to TAU. The control group will receive TAU alone. The post-treatment assessments will take place two weeks after the last EMDR session and six months later.

The primary outcome will be the change in the intensity of CBP within the last four weeks (numeric rating scale 0–10) from the pre-treatment assessment to the post-treatment assessment two weeks after the completion of treatment.

In addition, the patients will undergo a thorough assessment of the change in the experience of pain, disability, trauma-associated distress, mental co-morbidities, resilience, and quality of life to explore distinct treatment effects. To explore the mechanisms of action that are involved, changes in pain perception and pain processing (quantitative sensory testing, conditioned pain modulation) will also be assessed.

The statistical analysis of the primary outcome will be performed on an intention-to-treat basis. The secondary outcomes will be analyzed in an explorative, descriptive manner.

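### The primary analysis is labelled intention-to-treat, but a complete-case rule with an unsound justification excludes randomised patients who have no T1 value

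*Protocol article*

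**What the plan says.** The intention-to-treat principle is stated three times in the protocol article.

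- Abstract, Methods/design: "The statistical analysis of the primary outcome will be performed on an intention-to-treat basis".
- Sample size estimation: "The patients who are lost to follow up and/or non-compliant patients will be handled using an intention-to-treat procedure".
- Statistical analyses: the label is repeated for the data analysis as a whole.

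The Statistical analyses section then gives the operating rule. The premise is "Because of the small sample size in the study, multiple imputation (the gold standard for handling missing values) is not appropriate" and the conclusion is "Therefore, only complete cases will be used in the final analysis". The test is an independent-groups t-test on change scores, with no baseline covariate. The same section promises a detailed look at dropouts, withdrawals and missing values, and sensitivity analyses comparing several techniques.

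Under Sample size estimation the authors write "we expect a 20% drop-out rate". Under Outcome measures the primary endpoint is the change in back pain NRS from T0 to T1. Under Data acquisition T0 precedes randomisation, and T1 and T2 are planned assessments with no arm or patient excepted.

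**The concern.** For a patient lost before T1, the two instructions cannot both be followed. One section says such a patient is handled by intention-to-treat; the next leaves that patient out of the final analysis. A reader of the results would be told that all randomised patients are accounted for when about a fifth may not be.

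The justification is also faulty at both steps. A small sample does not by itself invalidate multiple imputation. Even if it did, complete cases would not follow, because likelihood-based and baseline-adjusted analyses would still be available.

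What is at stake is the primary estimate. One arm is asked to attend ten 90-minute trauma-focused sessions over 20 weeks and the other is not, so the reasons for leaving may well differ by arm. The protocol itself foresees that pain may be worse after the intervention than before, and plans to report this. If such patients leave before T1, the primary comparison does not see them.

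**Working it through.** **1. The plan's own figures.** Inputs from Sample size estimation: "A sample size of 17 patients in each group will have 80% power to detect an effect size of 1.0", "with a 0.05 two-sided significance level", 20% drop-out, and "a total sample size of 40 patients is required for the study". The noncentral-t calculation gives n = 16.71, so 17 per arm with power 80.7%. The 17 is reproduced.

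**2. Patients removed by the rule.** 0.20 × 40 = 8 excluded, leaving 32, or 16 per arm if losses are equal. Power at d = 1.0 is then 78.1%, against 86.9% with all 40 observed. Since 78.1% is within 2 points of 80%, the issue is bias, not power.

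**3. Who is removed.** A change score needs T0 and T1. T0 exists for everyone randomised, so the rule removes exactly those without T1. A patient who stopped sessions but attended T1 is kept and analysed as randomised.

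**4. Simple bias arithmetic.** If control losses are random, bias = share of the EMDR arm lost × gap in mean change between leavers and completers. With 20% lost and an assumed gap of 0.5 to 1.0 SD: 0.20 × 0.5 = 0.10 and 0.20 × 1.0 = 0.20 SD in favour of EMDR. The protocol gives no gap, so this is only a range.

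**5. Simulations under no true effect.** Assumptions: 20 per arm, baseline-to-T1 correlation 0.5, and unit SDs, so that the SD of change is √(1 + 1 − 2 × 0.5) = 1; about 20% missing. Multiple imputation (MI) used 20 imputations, a baseline-adjusted analysis and Barnard-Rubin degrees of freedom. ANCOVA is the complete-case analysis adjusted for baseline. Cells show bias in SD, then type I error. Negative values favour EMDR.

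| Assumed loss | Planned t-test | ANCOVA | MI |
|---|---|---|---|
| A. Completely random | 0.00; 5.9% | 0.00; 5.4% | 0.00; 5.3% |
| B. On baseline, opposite by arm, log-odds 1.2 per SD | +0.21; 8.8% | 0.00; 5.2% | 0.00; 4.7% |
| C. On baseline, opposite by arm, separate run | −0.18; 8.2% | about 0; 5.3% | not run |
| D. EMDR loss on the T1 value, log-odds 1.2 per SD | −0.10; 5.2% | −0.16; 7.2% | −0.16; 6.7% |
| E. EMDR loss on lack of improvement, log-odds 1 per SD | −0.17; 7.9% | −0.13; 7.4% | not run |
| F. The four worst-changing EMDR patients leave | −0.33; 19.1% | −0.26; 15.5% | not run |

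Rows A, B and D use 4,000 runs each, so the Monte Carlo standard error near 5% is √(0.05 × 0.95 / 4000) = 0.3 points. Other runs of the planned test under random loss gave 5.0% and 5.3%, so the 5.9% in row A should not be read as a defect.

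**6. Reading the table.**
- Rows A and B: MI holds its type I error at this sample size, which answers the stated reason for rejecting it.
- Rows B and C: this is the avoidable part. The bias can go either way, depending on which arm loses its high-baseline patients, and adjustment for T0 removes it.
- Rows D to F: this is the part that no missing-at-random analysis removes. In row D the planned test is even the less biased one.

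**The case against.** The strongest defence has four parts.

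- **Missing data are not ignored.** The protocol commits to examining dropouts in detail and to comparing techniques in sensitivity analyses. This stands, and not naming the techniques in an article is no fault. But sensitivity analyses leave the primary estimate and its label as they are.
- **Patients are still analysed as randomised, and non-compliant patients with a T1 value are kept.** This stands. A reader might infer that the plan amounts to a per-protocol analysis; the text does not support that. The contradiction is confined to patients without T1.
- **The attrition mechanism is assumed.** This also stands. The protocol gives a single overall drop-out rate and nothing by arm or reason. Nor does the planned test need data missing completely at random: drop-out rates may differ by arm without bias, provided loss within each arm is unrelated to the change score.
- **The replacement would not cure the worst cases.** Correct. A reader might take the 8% and 19% type I errors in rows E and F as the harm done by the complete-case rule and undone by a better model. They measure the risk from outcome-dependent drop-out itself, and most of that bias survives baseline adjustment.

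It is likewise tempting to argue that T2 makes the replacement strong. A patient lost before T1 will often lack T2 as well and contribute only T0. The gain is then mainly that of baseline adjustment, and in row B complete-case ANCOVA did as well as MI.

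**Conclusion.** The point holds in a limited form. The intention-to-treat label conflicts with the complete-case rule for randomised patients without T1, about 8 of 40 on the plan's own drop-out figure, and the small-sample reason does not justify the rule.

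The avoidable statistical cost is exposure to baseline-related loss that differs by arm: a bias of about 0.18 SD and a type I error of about 8%, in a scenario with an assumed correlation of 0.5 and an assumed loss mechanism. It is a risk, not a demonstrated bias; its direction is not known, and it vanishes if loss within each arm is unrelated to the change score. The documents do not support saying that the primary result will favour EMDR, or that one particular model is required.

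This should be fixed before analysis. It does not invalidate the design.

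**What to change.** Replace the complete-case sentence in Statistical analyses with a primary analysis that:

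- includes all randomised patients and adjusts for T0 NRS;
- states its missing-at-random assumption;
- uses either a likelihood-based repeated-measures model or multiple imputation by arm, with small-sample degrees of freedom.

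State that the T1 NRS, already scheduled for everyone, is sought from patients who stop sessions. This is the only measure here that reduces outcome-dependent loss directly. Keep complete cases as a sensitivity analysis, and add a reference-based or tipping-point analysis for loss that depends on the unseen outcome.

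If complete cases remain primary, adjust that analysis for baseline, drop the small-sample argument, and remove or qualify the intention-to-treat label in the Abstract, Sample size estimation and Statistical analyses.

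The cost is revised wording, some programming and a modelling assumption to state and defend. No extra patients or visits are needed.

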### Participants

Participants will be recruited from the southwestern district “Rhein-Neckar” of Germany, through subproject six [43] of the LOGIN consortium. Patients will be offered enrolment, when in addition to CBP they additionally fulfill the criteria for experienced psychological trauma (see Table 1). Recruitment will be done consecutively until a sample size of n = 40 patients is reached (control group: n = 20; intervention group: n = 20). Randomization will be done centrally with the established randomization program RANDI_2_[44,45] after patient inclusion by an independent person not involved in treatment or assessment. Allocation concealment will be ensured, as this person will not release the randomization code until the patient has been recruited into the trial, which takes place after all baseline assessments have been completed.

**Table 1 T1:** Inclusion and exclusion criteria

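### The primary test is an unadjusted t-test on change scores; adjusting for the baseline pain rating already collected would give more power and correct for chance baseline differences in pain at very small cost

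*Protocol article*

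**What the plan says.** The Protocol article is consistent on this point across three sections. Under Outcome measures, the primary endpoint "is the change in the intensity of back pain from T_0_ to T_1_ measured on a numeric rating scale". Under Sample size estimation, "A sample size of 17 patients in each group will have 80% power to detect an effect size of 1.0". That calculation assumes a two-sample t-test on a two-sided 5% level. Under Statistical analyses, "The differences between the change scores of the patient groups will be analyzed using independent t-tests".

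No section names a baseline covariate or an adjusted analysis. The only sensitivity analyses mentioned concern drop-outs, withdrawals and missing values. The covariate is available, however. Under Participants, the randomisation code is held back until recruitment of the patient, a step "which takes place after all baseline assessments have been completed", and Data acquisition likewise places T0 before randomisation.

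**The concern.** A change score subtracts the whole baseline value, which fixes the slope of T1 on T0 at 1. With similar variances at the two visits, the true slope equals the pre-post correlation r and so lies below 1. Two things follow.

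First, the change score carries more residual variance than an analysis that estimates the slope. This trial has little power to spare: it was sized at 80% for a large effect, and the complete-case analysis is expected to lose a fifth of the patients.

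Second, if one arm happens to start with higher pain, regression to the mean makes it appear to improve more. With about 16 patients per arm, and no stratification on pain described, a noticeable chance difference is quite possible. The single confirmatory comparison would then include a shift that the available data could have removed.

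**Working it through.** **Inputs from the Protocol article.** Two-sided alpha is 0.05 and the standardised effect is 1.0 (Sample size estimation: "an effect size of at least 1.0 can be expected after ten sessions of treatment"). Allocation is 20 and 20 (Design). On attrition, "we expect a 20% drop-out rate" (Sample size estimation). The final analysis uses complete cases (Statistical analyses). Completers: 40 × 0.8 = 32, or 16 per arm.

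**Assumptions.** The pre-post correlation r is not in the documents, so 0.3, 0.5 and 0.7 are shown. The variances at T0 and T1 are taken as equal and the baseline relation as linear.

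**1. The plan's own figure.** Two-sample t-test, noncentral t with noncentrality d / √(2/n) and 2n − 2 df:
- n = 17, d = 1.0: 1/√(2/17) = 2.92 on 32 df, power 80.7%. The stated 80% reproduces.
- n = 16, d = 1.0: 1/√(2/16) = 2.83 on 30 df, power 78.1%.

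**2. Variance with and without adjustment.** With s the SD at each visit:
- change score: 2s²(1 − r)
- ANCOVA residual: s²(1 − r²)
- ratio: (1 + r)/2 = 0.65, 0.75 and 0.85 for r = 0.3, 0.5 and 0.7.

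ANCOVA leaves 2n − 3 = 29 df at 16 per arm. Averaged over simulated chance baseline differences, estimating the slope inflates its variance by a factor of 1.034. Both costs are included below.

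**3. Power at 16 per arm, effect 1.0 in change-score SDs.**

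| r | t-test on change | ANCOVA | Effect detectable with 80% power, ANCOVA |
|---|---|---|---|
| 0.3 | 78.1% | 91.5% | 0.84 |
| 0.5 | 78.1% | 87.3% | 0.90 |
| 0.7 | 78.1% | 83.0% | 0.96 |

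The corresponding detectable effect for the t-test is 1.02. At r = 0.8, ANCOVA still has 80.9%. The two methods break even at r of about 0.93; at r = 0.95 ANCOVA has 77.7%.

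**4. The other reading of the effect size.** The article does not say which SD scales the 1.0. If it is the baseline (or T1) SD, the effect in change-score SDs is 1/√(2(1 − r)) = 0.85, 1.00 and 1.29, and power at 16 per arm is:

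| r | t-test on change | ANCOVA |
|---|---|---|
| 0.3 | 63.8% | 80.5% |
| 0.5 | 78.1% | 87.3% |
| 0.7 | 94.2% | 96.4% |

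**5. Shift from a chance baseline difference.** At 16 per arm the standard error of the baseline difference is √(2/16) = 0.35 SD. Given a difference of that size, the change-score contrast moves by (1 − r) × 0.354 = 0.25, 0.18 and 0.11 baseline SD for r = 0.3, 0.5 and 0.7, in favour of the arm that started higher.

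**The case against.** The strongest reply is that nothing here is wrong. Endpoint, sample size and test agree with one another. Under randomisation the change-score t-test is unbiased and keeps its type I error. All of that stands, and it limits the point to efficiency and precision.

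Some stronger readings are tempting but are not supported:
- **That the planned analysis is biased.** Averaged over randomisations it is not. The shift exists only conditionally on a realised baseline difference, and a prospective protocol contains no data showing one.
- **That the NRS is a single noisy rating, so r must be low.** Outcome measures describes intensity averaged over four weeks and does not say whether this is a recalled average or a mean of several ratings. Averaging would tend to raise r, where the gain is smallest.
- **That the trial's power is 64%.** That figure needs both the baseline-SD reading and r = 0.3. Sample size estimation refers to the change in pain, and on the change-score scale the t-test has 78.1% whatever r is.
- **That adjustment is free and deals with imbalance generally.** It uses one degree of freedom and about 3% in variance, and it corrects only linear imbalance in baseline NRS.

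It is also fair to say that the size of the gain rests on an assumed r. Its direction does not, short of r of about 0.93.

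**Conclusion.** The point holds as an avoidable inefficiency in the primary analysis. The article does not leave the choice open: it names an unadjusted test even though a pre-randomisation measurement of the same variable is available. At the expected 16 completers per arm, ANCOVA adds about 13, 9 or 5 percentage points of power at r = 0.3, 0.5 or 0.7 if the effect is 1.0 change-score SD. The gain is about 17, 9 or 2 points if the effect is 1.0 baseline SD. On the change-score scale it restores the intended 80% after drop-out for r up to about 0.8, without another patient. It also removes the conditional shift from a chance difference in baseline pain.

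These figures rest on the assumed r, similar variances at T0 and T1, a linear baseline relation, and drop-out of 20% spread evenly over the arms. The validity of the planned test is not in question.

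**What to change.** Under Statistical analyses, make the primary test an ANCOVA of T1 NRS on treatment arm with T0 NRS as covariate. Report the adjusted mean difference with its 95% CI, and keep the independent t-test on change scores as a supportive analysis. The endpoint definition can stay as it is, because ANCOVA of the change with T0 as covariate gives the identical treatment estimate. Settling this before the data are seen also prevents a later choice between adjusted and unadjusted results.

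The change is one of analysis wording. No further data or patients are needed, and no completer is lost, since anyone with a change score has a T0 value. The statistical cost is the one degree of freedom and roughly 3% variance already counted above. The calculation of 17 per group can stand and is conservative unless r is above about 0.93.
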